# DETECT I & DETECT II: a study protocol for a prospective multicentre observational study to validate the UroMark assay for the detection of bladder cancer from urinary cells

**DOI:** 10.1186/s12885-017-3758-7

**Published:** 2017-11-15

**Keywords:** Bladder cancer, Clinical trial, Diagnostic, Haematuria, Methylation, Next generation sequencing, Urinary assay, Urinary biomarker, Surveillance, Validation

## Abstract

**Background:**

Haematuria is a common finding in general practice which requires visual inspection of the bladder by cystoscopy as well as upper tract imaging. In addition, patients with non-muscle invasive bladder cancer (NMIBC) often require surveillance cystoscopy as often as three monthly depending on disease risk. However, cystoscopy is an invasive procedure which is uncomfortable, requires hospital attendance and is associated with a risk of urinary tract infection. We have developed the UroMark assay, which can detect 150 methylation specific alteration specific to bladder cancer using DNA from urinary sediment cells.

**Methods:**

DETECT I and DETECT II are two multi-centre prospective observational studies designed to conduct a robust validation of the UroMark assay. DETECT I will recruit patients having diagnostic investigations for haematuria to determine the negative predictive value of the UroMark to rule out the presence of bladder cancer. DETECT II will recruit patients with new or recurrent bladder cancer to determine the sensitivity of the UroMark in detecting low, intermediate and high grade bladder cancer. NMIBC patients in DETECT II will be followed up with three monthly urine sample collection for 24 months while having surveillance cystoscopy. DETECT II will include a qualitative analysis of semi-structured interviews to explore patients’ experience of being diagnosed with bladder cancer and having cystoscopy and a urinary test for bladder cancer surveillance. Results of the UroMark will be compared to cystoscopy findings and histopathological results in patients with bladder cancer.

**Discussion:**

A sensitive and specific urinary biomarker will revolutionise the haematuria diagnostic pathway and surveillance strategies for NMIBC patients. None of the six approved US Food and Drug Administration urinary test are recommended as a standalone test. The UroMark assay is based on next generation sequencing technology which interrogates 150 loci and represents a step change compared to other biomarker panels. This enhances the sensitivity of the test and by using a random forest classifier approach, where the UroMark results are derived from a cut off generated from known outcomes of previous samples, addresses many shortcomings of previous assays.

**Trial registration:**

Both trails are registered on clinicaltrials.gov. DETECT I: NCT02676180 (18th December 2015). DETECT II: NCT02781428 (11th May 2016).

## Background

Haematuria is a common finding in general practice [1] and requires visual inspection of the bladder by cystoscopy as well as upper tract imaging [2]. Both non-visible and visible haematuria are associated with the presence of bladder cancer [3]. However, bladder cancer is responsible for only 12.0% and 5.2% of visible and non-visible haematuria respectively [4]. Cystoscopy is an invasive procedure which is uncomfortable, requires hospital attendance and is associated with a 5% risk of urinary tract infection [5]. It is estimated that using cystoscopy to investigate haematuria cost the UK healthcare £55 million per year, ranking bladder cancer as one of the most expensive cancers to manage [6]. Furthermore, patients with known non-muscle invasive bladder cancer (NMIBC) will require surveillance cystoscopy as frequently as 3 monthly in high risk cases due to the risk of disease recurrence and progression of between 31%–78% and 17%–45% respectively within 5 years [7]. Hence, a non-invasive urinary test which can rule out the presence of bladder cancer would be of great value.

Two Health Technology Assessment (HTA) commissioned systematic reviews have highlighted the clinical need for urinary based markers for the detection of bladder cancer [8, 9]. Currently available Food and Drug Administration (FDA) approved urinary based markers have failed to become standard practice as they miss a significant number of patients with bladder cancer and are subject to a high number of false positives [10]. Hence, no urinary biomarker has been approved as a standalone test for the detection of bladder cancer and cystoscopy is still recommended.

Epigenetic alterations such as DNA methylation make an ideal non-invasive biomarker for the detection and surveillance of disease given its ontogenic plasticity and tissue specificity. A number of emerging assays based on epigenomic panels have shown the potential utility of DNA methylation changes as urinary biomarkers for the detection of bladder cancer [11, 12]. We have developed the UroMark assay, which can detect 150 methylated specific alteration using DNA from urinary sediment cells. Full details of the development of this assay has been described previously [13]. Unlike previous reported tests, the UroMark assay utilises microdroplet-based polymerase chain reaction (PCR) application followed by next-generation sequencing of amplification of target loci using RainDance Technology, which allows sensitive, specific and simultaneous amplification of up to 20,000 methylated loci [14–16]. DETECT I and DETECT II are two multi-centre prospective observational studies designed to conduct a robust validation of the UroMark assay.

## Methods/design

Both DETECT I and DETECT II are prospective multicentre observational study designed to assess the diagnostic performance of the UroMark. Both studies will recruit patients in >30 centres in the UK.

### Detect I

#### Objectives

The primary objective of DETECT I is to determine the negative predictive value of the UroMark assay to rule out the presence of bladder cancer in patients with haematuria. The secondary objectives include 1) to assess the feasibility of a large scale home urine collection system for high throughput analysis, 2) exploratory health economics analysis of patients’ views on the use of a urine based test and 3) to assess the negative predictive value and positive predictive value of the combination of standard of care imaging with the UroMark in the entire cohort and in pre-defined sub-groups of patients.

#### Study design

The study will recruit patients who are referred for haematuria investigations by their general practitioner (GP). Inclusion criteria include 1) patients ≥18 years of age, 2) undergoing cystoscopy for visible or non-visible haematuria, 3) had upper tract imaging (either ultrasound kidney, ureters and bladder (KUB), CT KUB or CT intravenous urogram (IVU)) within 12 weeks of registration into the study and 4) patients who are able to provide informed consent. Patients who are unwilling to have cystoscopy and upper tract imaging or unable to give informed consent will be excluded.

The study schedule for DETECT I is reported in Fig. 1. Written informed consent will be obtained and patients will be screened for eligibility and inclusion into the trial. Patients will be given a UroMark home urine collection kit and samples are mailed to the laboratory in a prepaid postage envelope in packaging specifically designed for this purpose, and approved by Royal Mail. Patients will have standard haematuria investigations which consist of flexible cystoscopy and upper tract imaging. They will also be asked to complete a health economics questionnaire which is designed to capture their opinion and perspectives on their confidence in having a specialised assay to diagnose their bladder cancer instead of cystoscopy. Patients with cystoscopic evidence of tumour will be treated with transurethral resection of bladder tumour (TURBT) as part of standard practice and histopathological evidence of tumour will be used a standard reference. All urine samples are collected prior to TURBT.

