#### Assessment

Patient demographics including age, gender, occupation, ethnicity and smoking history will be recorded. Results of flexible cystoscopy, upper tract and bladder imaging and histopathological results (if TURBT or bladder biopsy is performed) will be recorded in an electronic case report form (eCRF).

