#### Sample size and power calculations

The primary outcome of DETECT I is the negative predicted value (NPV) of the UroMark assay which is expected to be 98% (or higher). Using the exact binomial method, to give a lower bound for a 95% confidence interval of 96.75%, 800 negative test results are required. It is expected that 90% of all tests would be negative thus; we will require at least 889 evaluable urine samples. With this sample size, the uncertainty in the estimated NPV will be less than 1% if the NPV is higher than 98%. The data analysis will involve calculating the NPV from the data, along with an exact binomial confidence interval. To ensure confidence subjects will be recruited until at least 89 tumours have been detected. It is proposed that the NPV will be examined after a third of cases have been recruited (approximately 300 cases). If the NPV is substantially below that assumed, the study may be terminated early.

For the secondary outcome, the NPV of imaging (ultrasound KUB/CT) alone and the combination of imaging and the UroMark assay will be determined. Specifically, the NPV of UroMark will be calculated for the following subgroups: haematuria type (visible vs non-visible), gender (male vs female), age (≤50 vs >50 years) and smoking history (yes vs no). Fisher’s exact test will be used to determine the NPV.

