## Conclusion

DETECT I and II is a multi-centre prospective observational studies designed to conduct a robust validation of the UroMark assay. DETECT I will validate the ability of the UroMark assay to rule out bladder cancer in patients with haematuria while DETECT II will determine the diagnostic accuracy of the assay in a patient cohort enriched for low grade cancer and test the ability of the UroMark assay to detect bladder cancer recurrence. We aim to show sufficient diagnostic precision to replace cystoscopy in the evaluation of patients with haematuria. The incorporation of a highly sensitive and specific assay will revolutionise bladder cancer pathways, have a profound impact on the requirement for cystoscopy and on patient well-being and, reduce the healthcare costs associated with investigation of haematuria and surveillance for disease recurrence.

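### DETECT I describes only the index work-up as comparator, so a tumour missed by both cystoscopy and UroMark counts as a true negative and can only raise the primary NPV

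*Protocol article*

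**What the plan says.** The DETECT I Objectives state the primary aim: "The primary objective of DETECT I is to determine the negative predictive value of the UroMark assay" for ruling out bladder cancer in patients with haematuria. The sample size section gives the outcome as the "negative predicted value (NPV) of the UroMark assay which is expected to be 98% (or higher"), to be reported with an exact binomial interval.

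On disease status, the DETECT I Study design says that every patient has flexible cystoscopy and upper tract imaging. Patients with a visible tumour go to TURBT, and for them "histopathological evidence of tumour will be used a standard reference". The DETECT I Assessment section records the cystoscopy result, upper tract and bladder imaging, and "histopathological results (if TURBT or bladder biopsy is performed"). The Methods paragraph of the abstract sets UroMark against what cystoscopy shows and, where cancer is present, against histology.

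Follow-up, with urine samples every 3 months for 24 months, is described only for NMIBC patients in DETECT II. The Conclusion gives the intended use: "We aim to show sufficient diagnostic precision to replace cystoscopy in the evaluation of patients with haematuria".

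**The concern.** An NPV needs a disease status for every UroMark-negative patient, about 800 people here. Most of them will have no visible tumour and no histology. For these patients the only comparator described is the index work-up, which is led by the test that UroMark is meant to replace.

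The two kinds of cystoscopy miss act differently:

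- **Missed by both tests.** The patient is really a false negative but is scored as a true negative. NPV rises.
- **Missed by cystoscopy, UroMark-positive.** The patient is scored as a false positive. NPV is unchanged, because the patient is not among the negative tests, and PPV falls. A secondary objective uses PPV, for UroMark combined with imaging.

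The effect on the primary outcome therefore goes one way only. The exact interval covers sampling error and not this misclassification. The reported NPV could be read as the probability of having no bladder cancer, when it is the probability that the index work-up finds none.

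**Working it through.** **Inputs from the DETECT I sample size section.** The expected NPV is 98%. The precision target reads "to give a lower bound for a 95% confidence interval of 96.75%, 800 negative test results are required". The share of negative results is put at 90%, from which the section derives its total: "we will require at least 889 evaluable urine samples". Recruitment runs on until 89 or more tumours have been found.

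**The plan's own figures.**
- At 98%, 800 negatives contain 0.98 × 800 = 784 true negatives and 16 false negatives. The two-sided 95% exact (Clopper-Pearson) interval for 784/800 is 96.77% to 98.85%, against the stated lower bound of 96.75%.
- Samples: 800 / 0.90 = 888.9, rounded up to 889.
- Tumours: 10% of 889 = 88.9, which matches 89.

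The sample size arithmetic reproduces and is not in question.

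**Effect of m tumours missed by both tests.** True NPV = (784 − m) / 800.

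| m | True NPV | Exact lower limit |
|---|---|---|
| 0 | 98.00% | 96.77% |
| 1 | 97.88% | 96.62% |
| 5 | 97.38% | 96.02% |
| 8 | 97.00% | 95.57% |
| 10 | 96.75% | 95.27% |

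One such tumour takes the lower limit below the planned 96.75%.

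**How large m might be.** This needs two quantities that the documents do not give, so both are assumptions:
- c, the sensitivity of cystoscopy, taken as 98%, 95%, 90% or 85%. Tumours missed by cystoscopy = 89/c − 89.
- q, the share of those that UroMark also misses. Independent errors give q = 16/89 = 18%, the UroMark miss rate among detected tumours. The other values are 50% and 100%.

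Then m = q × (89/c − 89) and the inflation is m/800. For example, at c = 90%: 89/0.90 − 89 = 9.9 missed. With q = 50%, m = 4.9, the inflation is 4.9/800 = 0.62 points and the true NPV is 97.38%.

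Each cell gives true NPV, with the exact lower limit in brackets (m need not be a whole number).

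| c | Missed by cystoscopy | q = 18% | q = 50% | q = 100% |
|---|---|---|---|---|
| 98% | 1.8 | 97.96% (96.72%) | 97.89% (96.63%) | 97.77% (96.50%) |
| 95% | 4.7 | 97.89% (96.64%) | 97.71% (96.42%) | 97.41% (96.06%) |
| 90% | 9.9 | 97.78% (96.50%) | 97.38% (96.02%) | 96.76% (95.29%) |
| 85% | 15.7 | 97.65% (96.34%) | 97.02% (95.59%) | 96.04% (94.44%) |

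Inflation over c = 98% to 85%:
- q = 18%: 0.04 to 0.35 points
- q = 50%: 0.1 to 1.0 points
- q = 100%: 0.2 to 2.0 points

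**The case against.** **The article is condensed.** It nowhere says in words that cystoscopy-negative patients count as cancer-free, Fig. 1 is not shown, and the full protocol may contain a later check. This stands: a reader might infer that the trial has no later check, and the documents do not establish that. What can be said is that the article states its comparator and its recorded data, and neither points to such a check.

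**Histology is not tied to a positive cystoscopy.** A reader might infer that histology is obtained only when cystoscopy shows a tumour. The Assessment section does not say so. It records histology from any bladder biopsy and also records bladder imaging, so some cystoscopy misses could surface at the index work-up. This stands, and to that extent c should be read as the sensitivity of the whole work-up. But that check is concurrent, not later, and the text does not name imaging as part of the reference standard.

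**The size is assumed.** This also stands. Under independent errors the inflation is at most 0.35 points over the range shown. The 1.0 and 2.0 point figures need low cystoscopy sensitivity together with strongly shared misses. Independence is not documented either. The article reports that existing urinary markers are more sensitive in high grade and high stage tumours. If cystoscopy also tends to miss the tumours that UroMark finds hard (an assumption), the misses are shared.

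**Tumours missed by both tests are missed on either pathway.** True, so they do not alter a comparison of UroMark with cystoscopy. They do alter an NPV presented as ruling out bladder cancer. This argues for labelling the NPV as relative to the index work-up.

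**Conclusion.** The point holds as a limit on what the primary NPV means. With the comparator as described, tumours missed by both tests can only push NPV upward, and the planned interval does not show it. The direction follows from the definition of NPV. The size does not follow from the documents: 0.04 to 2.0 points across the assumed cystoscopy sensitivities of 98% to 85% and the three assumptions about shared misses, with the low end applying if errors are independent and cystoscopy misses little.

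A reader might infer that a plausible miss rate would use up the trial's margin. That is not supported. The 1.25 points from 98% to 96.75% are a planned precision, the section states no pass mark for the final NPV, and no miss rate is given. The comparison shows only that the bias could be of the same order as the stated uncertainty. This is a cheap improvement to the analysis and its wording, not an error in the sample size.

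**What to change.** 1. Keep the primary NPV, but define it as NPV relative to the index work-up (cystoscopy, imaging and any histology).
2. Pre-specify a tipping-point table of NPV and its exact lower limit over assumed cystoscopy sensitivity and the share of its misses that UroMark also misses.
3. Add one eCRF field, completed from routine centre records available at database lock, for any bladder cancer diagnosed after a negative index cystoscopy. Report a second NPV that counts these as reference-positive, with the length of follow-up shown.
4. Make a claim about replacing cystoscopy only if these analyses agree. Otherwise word the conclusion relative to the index work-up.

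If the full protocol already contains a later check, citing it and using it in step 3 is enough.

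**Cost.** One look-up field per patient and two extra analyses, with no added procedure and no larger sample. The downsides are data entry at the centres, incomplete capture of cancers diagnosed elsewhere, shorter follow-up for late recruits, some new cancers mixed with missed ones, and a possibly less favourable NPV. Requiring a fixed window would instead cost time: with recruitment expected to close on 1 February 2019, a 12-month window would move the last look-up to about February 2020.

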**Fig. 1 Fig1:**
[figure not shown]
Study schedule for DETECT I

The study protocol was approved by Health Research Authority: North West Liverpool Central Research Ethics Committee on the 9 ^th^ March 2016 (IRAS project ID: 179,245, REC reference: 16/NW/0150). DETECT I is registered on clinicaltrials.gov NCT02676180.

#### Assessment

Patient demographics including age, gender, occupation, ethnicity and smoking history will be recorded. Results of flexible cystoscopy, upper tract and bladder imaging and histopathological results (if TURBT or bladder biopsy is performed) will be recorded in an electronic case report form (eCRF).

#### Sample size and power calculations

The primary outcome of DETECT I is the negative predicted value (NPV) of the UroMark assay which is expected to be 98% (or higher). Using the exact binomial method, to give a lower bound for a 95% confidence interval of 96.75%, 800 negative test results are required. It is expected that 90% of all tests would be negative thus; we will require at least 889 evaluable urine samples. With this sample size, the uncertainty in the estimated NPV will be less than 1% if the NPV is higher than 98%. The data analysis will involve calculating the NPV from the data, along with an exact binomial confidence interval. To ensure confidence subjects will be recruited until at least 89 tumours have been detected. It is proposed that the NPV will be examined after a third of cases have been recruited (approximately 300 cases). If the NPV is substantially below that assumed, the study may be terminated early.

For the secondary outcome, the NPV of imaging (ultrasound KUB/CT) alone and the combination of imaging and the UroMark assay will be determined. Specifically, the NPV of UroMark will be calculated for the following subgroups: haematuria type (visible vs non-visible), gender (male vs female), age (≤50 vs >50 years) and smoking history (yes vs no). Fisher’s exact test will be used to determine the NPV.

### DETECT II

#### Objectives

The primary objective of DETECT II is to determine the sensitivity of the UroMark to detect new and recurrent low, intermediate and high grade bladder cancer. Secondary objectives include 1) to determine whether the UroMark can detect NMIBC recurrence in patients undergoing cystoscopic surveillance for bladder cancer, 2) to assess patients’ perspectives on cystoscopy and using a non-invasive urinary test and 3) to use semi-structured patient interviews to qualitatively explore patients experience of being diagnosed with bladder cancer and having cystoscopy and a non-invasive urinary test as a method of bladder cancer surveillance.

#### Study design

The study will recruit patients with new or recurrent bladder cancer. Patients who are not willing to have TURBT or unable to give consent will be excluded.

The DETECT II study schedule is reported in Fig. 2. Patients will be screened and included into the trial at flexible cystoscopy after visual confirmation of new or recurrent bladder tumour. Written consent will then be obtained from eligible patients. A baseline urine sample will be collected using the same home urine collection kit being used in DETECT I. Urine collection must be performed prior to TURBT. Histopathological confirmation of tumour stage (Ta, T1, ≥T2) and grade (G1, G2, G3) with or without CIS, or isolated CIS will be used a reference standard.

**Fig. 2 Fig2:**
[figure not shown]
Study Schedule DETECT II

All patients will receive standard test and investigations for bladder cancer. Following a TURBT, it is recommended that patients with NMIBC will receive a single instillation of intravesical chemotherapy unless clinically contraindicated. Intermediate risk NMIBC will have an inductive course of intravesical chemotherapy post TURBT while high risk NMIBC may require a repeat TURBT, usually within 6 weeks of the first TURBT. The repeat resection is recommended for high risk tumours to exclude residual detrusor muscle invasion (pT2 at least). High risk patients will either have an inductive and maintenance course of intravesical BCG or a radical cystectomy. This is consistent with international consensus [17].

Patients with NMIBC will have periodic cystoscopic surveillance following TURBT between 3 to 12 month intervals depending on disease risk in accordance to local hospital guidelines. Patients will be asked to provide a urine sample using a UroMark urinary collection kit every 3 months for 24 months (Table 1). It is important that urine samples are collected prior to TURBT to capture urine positive for recurrent tumour.

**Table 1 Tab1:** Table of Assessments in DETECT II

Visit	Baseline Before TURBT	3 Month	6 Month	9 Month	12 Month	15 Month	18 Month	21 Month	24 Month
Inclusion criteria	X								
Smoking history	X								
Visual Diagnosis of bladder cancer	X								
Surveillance Cystoscopy:									
Low risk		X			X				
Intermediate risk		X		X			X		
High risk		X	X	X	X	X	X	X	X
UroMark Test	X	X	X	X	X	X	X	X	X

NMIBC patients undergoing surveillance will complete a questionnaire designed to assess their perspectives on cystoscopy compared with a urinary test as part of surveillance to detect bladder cancer recurrence (Table 1). Selected patients will be invited for a telephone interview to further explore their experience of being diagnosed with bladder cancer and having cystoscopy and a urinary test as a method of bladder cancer surveillance. Up to 40 patients will participate in a qualitative analysis of semi-structured interviews but this number may be lower if patient responses have reached a saturation point. Patients will be interviewed after a minimum of 6 months’ follow-up to ensure all patients will be able to provide an informed opinion after having both diagnostic investigations: cystoscopy and urine based test.

DETECT II study protocol received Health Research Authority: London- Stanmore Research Ethics Committee approval on the 30th August 2016 (IRAS project ID: 203,022, REC reference: 16/LO/1044). This trial is registered on clinicaltrials.gov NCT02781428.

